# Financial incentives to motivate treatment for hepatitis C with direct acting antivirals among Australian adults (The Methodical evaluation and Optimisation of Targeted IncentiVes for Accessing Treatment of Early-stage hepatitis C: MOTIVATE-C): protocol for a dose-response randomised controlled study

**DOI:** 10.1186/s13063-024-08212-8

**Published:** 2024-06-17

**Keywords:** Randomised study, Dose–response, Bayesian design, Adaptive study, Direct-acting antiviral, Financial incentives, Hepatitis C, Primary care

## Abstract

**Background:**

Untreated hepatitis C virus (HCV) infection can result in cirrhosis and hepatocellular cancer. Direct-acting antiviral (DAA) therapies are highly effective and have few side effects compared to older interferon-based therapy. Despite the Australian government providing subsidised and unrestricted access to DAA therapy for chronic HCV infection, uptake has not been sufficient to meet the global target of eliminating HCV as a public health threat by 2030. This study will offer people with HCV financial incentives of varying values in order to evaluate its effect on initiation of DAA therapy in primary care.

**Methods:**

Australian adults (18 years or older) who self-report as having current untreated HCV infection can register to participate via an automated SMS-based system. Following self-screening for eligibility, registrants are offered a financial incentive of randomised value (AUD 0 to 1000) to initiate DAA therapy. Study treatment navigators contact registrants who have consented to be contacted, to complete eligibility assessment, outline the study procedures (including the requirement for participants to consult a primary care provider), obtain consent, and finalise enrolment. Enrolled participants receive their offered incentive on provision of evidence of DAA therapy initiation within 12 weeks of registration (primary endpoint). Balanced randomisation is used across the incentive range until the first analysis, after which response-adaptive randomisation will be used to update the assignment probabilities. For the primary analysis, a Bayesian 4-parameter EMAX model will be used to estimate the dose–response curve and contrast treatment initiation at each incentive value against the control arm (AUD 0). Specified secondary statistical and economic analyses will evaluate the effect of incentives on adherence to DAA therapy, virological response, and cost-effectiveness.

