### Trial design {8}

MOTIVATE-C is a pragmatic, factorial, dose–response study that includes sequential analyses and Bayesian adaptive design elements including stopping rules and response-adaptive randomisation. The design has a fixed ‘dose’ (incentive) range for participant incentives, from AUD 0 to AUD 1000 in AUD 50 increments with the AUD 0 dose used as the reference/control dose. For prescribers, the amount of the co-incentive is either AUD 0 or AUD 100.

At the time of registration for the study, participants are randomised to one of the participant incentive amounts. The randomisation weights are balanced across the available incentive amounts until the first interim analysis. While the zero dose retains a fixed allocation weight over the duration of the study, the remaining allocation weights are updated proportional to the updated probabilities that each arm (incentive amount) exceeds a minimal effective dose criterion and that the incentive amounts have a greater probability of response than lower value incentives. The minimum effective dose (MED) criterion is achieved if there is a 0.95 probability that a particular incentive amount results in a ten-percentage point increment (in absolute terms) above the response on the control arm (AUD 0). Futile doses (incentive amounts) are those that have a probability of < 0.2 of being minimally effective and will exit the randomisation which ceases further enrolment to these incentive amounts. If the probability of the MED criterion met is < 0.2 for all incentive amounts, then enrolment will be suspended to consider redesign, necessitating protocol and analysis plan updates.

The design involves regular analyses, which start once all participants enrolled in the first 6 months have reached 12 weeks post-registration, and then every 4 months or after the commitment of AUD100,000, whichever occurs sooner. These analyses will estimate the dose–response curve by fitting a four-parameter EMAX model and calculating the posterior probability of response for all arms. The study will continue until the total study funds available for incentives for participants, co-incentives for nominated primary care prescribers, and compensatory payments (described below) have been expended. A final analysis will be undertaken at the end of the study to address secondary objectives and undertake the economic analyses.

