#### Secondary endpoints

Evidence of having had a HCV PCR test (regardless of result) within 12 weeks (84 days) of registrationNumber of scheduled/recommended days in which DAA therapy was not taken, irrespective of the prescribed duration of therapy (i.e. 8 weeks or 12 weeks):◦ < 7 days,◦ 7–13 days,◦ 14–20 days,◦ 21–27 days,◦ 28 + days,as self-reported (via SMS or to the navigator) at approximately 28 days after the expected end date of therapy (DAA therapy usually has a duration of 2–3 months).Sustained virological response (SVR), defined as a negative HCV RNA PCR test at any time from at least 4 weeks (28 days) after completion of DAA therapy and before 12 months after registration.

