#### Follow-up

Following confirmation that DAA has been dispensed, the participant is informed that they will be contacted in:(i)2–4 weeks following treatment initiation to confirm their receipt of the compensation + / − incentive payment and to document any untoward health-related events, and(ii)4–5 weeks after the expected date of completion of DAA therapy to facilitate a follow-up appointment with their treatment prescriber to test for a viral response (negative HCV PCR at least 28 days after completing therapy). At this end of treatment follow-up, the navigator also confirms and documents the participant’s self-reported adherence to treatment (recalled number of missed days of medication).

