## Assignment of interventions: blinding

### Who will be blinded {17a}

Participants are unblinded to the intervention as the primary research question is predicated on their knowledge of the assigned incentive value (dose). Similarly, nominated preferred prescribers are unblinded as the secondary research question is again predicated on the prescriber’s knowledge of the co-incentive value. While treatment navigators are not aware of the registrant’s assignment prior to making contact, in most cases they become unblinded due to the extent of their interaction with the participant. Prescribers may also become aware of the value of any incentive assigned to a participant they treat if the participant volunteers this information.

The study statistician needs to access participant level data for the purposes of conducting analyses and budget tracking and is therefore also unblinded. Other operational staff are not privy to the individual assigned incentive amounts but will be aware of the number of enrolled participants and aggregated summaries of the total budget expended on incentives and compensatory payments.

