Methods for secondary analyses include logistic and cumulative logit models (assuming proportional odds). An economic analysis will be used to identify an optimal incentive via a cost-effective analysis taking a health services perspective. Cost-effectiveness measures will be summarised as incremental cost-effectiveness ratios and net monetary benefit [15].

All analyses will be undertaken in a Bayesian framework with standard diagnostics run on MCMC chains and using posterior predictive checks for goodness of fit. Additional models may be investigated (and reported as post hoc) as sensitivity and stability checks.

A complete statistical analysis plan will be published separately in accordance with suggested guidelines [16].

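### Missed-day adherence has no value for people who never start, so comparing it across incentive amounts is a starters-only contrast that cannot show an effect of the incentive

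*Protocol article*

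**What the plan says.** - **Aim.** The Abstract (Methods) states: "Specified secondary statistical and economic analyses will evaluate the effect of incentives on adherence to DAA therapy, virological response, and cost-effectiveness".
- **Order of events.** Trial design {8}: "At the time of registration for the study, participants are randomised to one of the participant incentive amounts". The amount is then disclosed. Section {17a} says of blinding: "Participants are unblinded to the intervention as the primary research question is predicated on their knowledge of the assigned incentive value (dose". The decision to start therapy comes afterwards, and starting within 12 weeks is the primary endpoint.
- **Adherence endpoint.** Outcomes {12} defines it as scheduled treatment days not taken, in five ordered categories from under 7 days to 28 or more, self-reported "at approximately 28 days after the expected end date of therapy". There is no category for a person who never started.
- **Who is asked.** Follow-up: "Following confirmation that DAA has been dispensed, the participant is informed that they will be contacted". The missed-days question belongs to this post-dispensing contact.
- **Model.** Statistical methods {20a}: "Methods for secondary analyses include logistic and cumulative logit models (assuming proportional odds". Adherence is the only ordered endpoint listed, so the cumulative logit model must be meant for it.
- **SVR.** Defined as "a negative HCV RNA PCR test at any time from at least 4 weeks (28 days) after completion of DAA therapy", with an outer limit at 12 months after registration. No denominator is stated.
- **Missing data.** Section {20c} treats non-enrolment, or no evidence of commencement, as failure of the intervention. It does not mention adherence or SVR.

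**The concern.** The randomised groups are registrants. People with a missed-days value are the subset who went on to start, and membership of that subset is what the incentive is designed to alter. At AUD 0 the starters are people who needed no payment. At higher amounts they are a mixture of such people and others brought in by the money. A difference in adherence between amounts may then reflect only who was recruited into treatment, with no change in anyone's behaviour on treatment.

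The article gives reason to expect such a mixture. Its section on behavioural economics expects payment to reach people for whom education was not enough, and it ties payment to dispensing instead of to adherence or completion. Whether the added starters take their tablets is therefore a natural policy question. A starters-only model reported as an effect of incentives would answer it misleadingly: a useful amount could be reported as worsening adherence.

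**Working it through.** The article gives no sample size, power or expected effect for adherence, so there is no figure of its own to reproduce on this point.

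**Step 1: is the starters-only set forced by the text?** For adherence, yes. A person with no course of therapy has no scheduled days, fits none of the five categories, and is never asked. The cumulative logit model can be fitted only to starters unless the endpoint is changed.

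**Step 2: size, by a two-group mixture.**

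Inputs from Sample size {14}: initiation p0 = 15% at AUD 0 and p1 = 15% + 20 points = 35% at a high amount.

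Assumed, not in the article:
- a = share missing under 7 days among those who would start without an incentive;
- m = the same share among the added starters;
- nobody who would start at AUD 0 is deterred by a higher offer;
- the incentive changes nobody's own adherence.

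Formulas:
- Among starters at the high amount: (p0·a + (p1 − p0)·m) / p1, against a at AUD 0.
- Among all randomised: p0·a + (p1 − p0)·m, against p0·a at AUD 0.

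With a = 90% and m = 70%:
- Starters: (0.15 × 0.90 + 0.20 × 0.70) / 0.35 = 0.275 / 0.35 = 78.6%, against 90%. The apparent loss is 11.4 points.
- All randomised: 27.5% against 0.15 × 0.90 = 13.5%. The gain is 14 points.

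The apparent loss is produced entirely by composition, since no individual's adherence was changed.

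**Step 3: range over the assumptions.**

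| p1 | a | m | Starters, AUD 0 → high | All randomised, AUD 0 → high |
|---|---|---|---|---|
| 35% | 90% | 70% | 90% → 78.6% | 13.5% → 27.5% |
| 35% | 90% | 80% | 90% → 84.3% | 13.5% → 29.5% |
| 35% | 85% | 75% | 85% → 79.3% | 12.75% → 27.75% |
| 35% | 90% | 90% | 90% → 90% | 13.5% → 31.5% |
| 25% | 90% | 70% | 90% → 82.0% | 13.5% → 20.5% |

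The last row uses the 10-point increment that the article takes as minimally effective: (0.135 + 0.10 × 0.70) / 0.25 = 0.205 / 0.25 = 82.0%. When m = a the bias vanishes. If m exceeded a, the starters-only contrast would err in the other direction.

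**Step 4: precision.** The AUD 0 weight is fixed, but its later value is not given. If it stays at 1/21 (assumed), the stated range of 580 to 2000 gives 580/21 ≈ 28 to 2000/21 ≈ 95 people at AUD 0, and at 15% about 4 to 14 starters. The lower end is approximate, because 580 is the expected size in the null scenario. A starters-only contrast with control would rest on very few people.

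**Step 5: does the same hold for SVR?** Not from the text. SVR is a yes/no event whose window runs "after completion of DAA therapy and before 12 months after registration". A registrant who is never treated can be scored as not achieved, and no section confines the analysis to starters. What is open is the denominator, and the two possible choices can point in opposite directions.

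**The case against.** The strongest reply is that the article names model families, not analysis sets, and defers to a separate analysis plan that is not shown. Whom navigators follow up does not fix who is in a denominator. That stands for SVR. It does not stand for adherence, where the endpoint as worded excludes non-starters and no choice of model undoes that.

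A second reply is that describing adherence among people paid to start is legitimate, and that the specific questions under Objectives {7} concern initiation, dose-response and cost. This is right, and it is why a descriptive table is an adequate remedy. The Abstract, however, promises an effect of incentives on adherence, which such a table cannot deliver.

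A third reply is that an all-registrant version of adherence would largely repeat the primary outcome, since at 15% to 35% initiation some 65% to 85% of registrants would be non-starters. That is true and is a reason to interpret the composite modestly. It does not make the starters-only contrast a randomised one.

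Finally, the adherence rates in added starters are assumed. That also stands: the article gives none, so the figures show what can happen and are not a forecast.

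**Conclusion.** The point holds for adherence. As defined and modelled, the comparison across amounts conditions on the primary outcome and cannot support a statement about the effect of incentives on adherence. In the article's 15% to 35% scenario, the apparent change among starters is −11.4 points with assumed rates of 90% and 70%, −5.7 points with 90% and 80%, and nil with equal rates. Meanwhile the share of all registrants who start and adhere rises by 14 to 18 points.

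Four stronger readings are tempting and are not supported:
- **That SVR too exists only in starters.** Its window ends at a time counted from registration, it can be scored for everyone randomised, and section {20c} leans towards counting non-starters as failures without settling the matter. For SVR this is a request to confirm the denominator.
- **That the adherence endpoint also requires completion of therapy.** It is asked after the expected end date, whether or not the course was finished.
- **That the economic conclusion is pulled the wrong way.** No section says the economic model ignores initiation. Initiation multiplied by the rate among starters returns the registrant-level figure: 0.35 × 78.6% = 27.5%.
- **That cures double as a general result.** This needs the full 20-point increment and a high enough SVR in added starters. At 10 points, with an assumed 95% SVR in those who would start anyway and 75% to 95% in added starters, cures go from 14.25% to 21.75%–23.75% of registrants, a 1.53- to 1.67-fold rise.

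**What to change.** 1. Report adherence among starters by amount as a descriptive table, stating that the groups compared are not protected by randomisation, and make no claim of an incentive effect from it. Amend the Abstract's aim to match.
2. If a randomised comparison is wanted, use a composite in all randomised registrants: started within 12 weeks and missed under 7 days, yes or no. Model it by amount as for the primary endpoint. State how starters with no adherence report are scored.
3. Confirm that SVR is compared across amounts in all randomised registrants, with non-starters and undocumented SVR counted as not achieved.

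The cost is wording in the analysis plan and one additional binary model; no new data are needed. The downsides are that the absolute SVR rate will be lower, because starters who are not tested count as no SVR, and that the composite will mostly track initiation and should be read alongside the descriptive table.

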**Discussion:**

This project seeks to gain an understanding of the dose–response relationship between incentive value and DAA treatment initiation, while maximising the number of people treated for HCV within fixed budget and time constraints. In doing so, we hope to offer policy-relevant recommendation(s) for the use of financial incentives as a pragmatic, efficient, and cost-effective approach to achieving elimination of HCV from Australia.

**Trial registration:**

ANZCTR (anzctr.org.au), Identifier ACTRN12623000024640, Registered 11 January 2023 (https://anzctr.org.au/Trial/Registration/TrialReview.aspx?id=384923&isReview=true).

## Administrative information

Note: the numbers in curly brackets in this protocol refer to SPIRIT checklist item numbers. The order of the items has been modified to group similar items (see http://www.equator-network.org/reporting-guidelines/spirit-2013-statement-defining-standard-protocol-items-for-clinical-trials/)

Role of sponsor {5c}	The study sponsor and funder did not contribute to the study design and will not be involved in the conduct of the study or in the analyses of the results.

## Introduction

### Background and rationale {6a}

Hepatitis C virus (HCV) infection causes acute and chronic forms of hepatitis. In chronic HCV infection the disease may progress through worsening liver fibrosis to decompensated cirrhosis and/ or hepatocellular carcinoma and the need for liver transplantation [1]. HCV elimination is theoretically achievable thanks to the development of highly effective direct-acting antiviral (DAA) therapies for HCV infection. DAA therapies are associated with a viral cure rate of above 90% regardless of cirrhosis status, with significant improvement in liver function and reduced progression to hepatocellular cancer and end stage liver disease [2, 3]. Compared to older interferon-based therapy, DAA treatment is short (8–12 weeks vs 6–12 months) and has few side effects [4]. In March 2016, Australia became one of the first countries to make DAA therapy broadly accessible to adults with chronic HCV infection. Between March 2016 and December 2022, an estimated 100,684 people living with HCV infection initiated treatment [5]. However, after an initial surge in uptake of DAA therapy, treatment rates have fallen, and an estimated 74,400 Australians remained untreated at the end of 2022 [5].

Pragmatic strategies are needed to ensure people with early-stage chronic HCV infection access DAA therapy to prevent transmission and to avoid the debilitating and costly consequences of late-stage liver disease. Many people with HCV infection are socially marginalized and have difficulty accessing healthcare [5, 6]. Navigation by peers or other support workers has been shown to help people with complex health needs to access and adhere to care, including people with HCV [6].

Direct financial incentives have been shown to be beneficial for improving some desirable health-related behaviours, including vaccine uptake, cessation of smoking, and short-term treatment adherence [7, 8]. However, to date, few studies [9–12] have evaluated the use of financial incentives for short course HCV treatment and there is uncertainty regarding what value of incentives may be required to motivate initiation of DAA therapy. We postulate that a dose–response (incentive vs initiation of therapy) relationship exists and that characterising this relationship is needed to inform the incentivisation of HCV treatment.

The **M**ethodical evaluation and **O**ptimisation of **T**argeted **I**ncenti**V**es for **A**ccessing **T**reatment of **E**arly-stage hepatitis **C** (MOTIVATE-C) study is a novel dose-ranging study that aims to evaluate the effect of financial incentives on the propensity of people with chronic HCV infection to initiate DAA therapy in the context of a navigator-led patient support program.

### Objectives {7}

The primary aim of MOTIVATE-C is to implement, evaluate, and optimise the use of financial incentives to motivate initiation of DAA therapy in primary care settings among people with chronic HCV infection. Specific questions, in the context of a patient support program, are:Does offering a financial incentive to people with HCV to initiate DAA therapy in primary care increase the probability of treatment initiation compared to usual care (no incentive)?What is the dose–response relationship for the range of financial incentives offered and the probability of treatment initiation?What participant incentive is optimal in terms of minimising the costs expended under the incentive program relative to the costs averted from the progression of untreated chronic HCV?

The secondary aim of MOTIVATE-C is to examine the extent to which primary care provider co-incentives modify the probability of treatment initiation. Specific research questions for this aim are:Does offering primary care providers a co-incentive payment modify the probability of treatment initiation?How is the dose–response relationship modified by a co-incentive offered to the primary care provider?What combination of participant and primary care provider incentive is optimal in terms of minimising the costs expended under the incentive program relative to the costs averted from the progression of untreated chronic HCV infection?

### Trial design {8}

MOTIVATE-C is a pragmatic, factorial, dose–response study that includes sequential analyses and Bayesian adaptive design elements including stopping rules and response-adaptive randomisation. The design has a fixed ‘dose’ (incentive) range for participant incentives, from AUD 0 to AUD 1000 in AUD 50 increments with the AUD 0 dose used as the reference/control dose. For prescribers, the amount of the co-incentive is either AUD 0 or AUD 100.

At the time of registration for the study, participants are randomised to one of the participant incentive amounts. The randomisation weights are balanced across the available incentive amounts until the first interim analysis. While the zero dose retains a fixed allocation weight over the duration of the study, the remaining allocation weights are updated proportional to the updated probabilities that each arm (incentive amount) exceeds a minimal effective dose criterion and that the incentive amounts have a greater probability of response than lower value incentives. The minimum effective dose (MED) criterion is achieved if there is a 0.95 probability that a particular incentive amount results in a ten-percentage point increment (in absolute terms) above the response on the control arm (AUD 0). Futile doses (incentive amounts) are those that have a probability of < 0.2 of being minimally effective and will exit the randomisation which ceases further enrolment to these incentive amounts. If the probability of the MED criterion met is < 0.2 for all incentive amounts, then enrolment will be suspended to consider redesign, necessitating protocol and analysis plan updates.

The design involves regular analyses, which start once all participants enrolled in the first 6 months have reached 12 weeks post-registration, and then every 4 months or after the commitment of AUD100,000, whichever occurs sooner. These analyses will estimate the dose–response curve by fitting a four-parameter EMAX model and calculating the posterior probability of response for all arms. The study will continue until the total study funds available for incentives for participants, co-incentives for nominated primary care prescribers, and compensatory payments (described below) have been expended. A final analysis will be undertaken at the end of the study to address secondary objectives and undertake the economic analyses.

